**Fig. 2 Fig2:**
[figure not shown]
Overview of the DemStepCare intervention (medication analyses by the pharmacy and communication via the electronic case record are not shown to ensure clarity)

In addition, clinical pharmacists regularly conduct structured medication reviews with the aim of improving the quality and safety of the drug therapy. The attending GPs are alerted to inappropriate medication and drug-related problems (DRP).

Communication between the different parties (i.e. GPs, case managers, outpatient clinic, pharmacy) takes place via a specifically adapted electronic case record. Thus, timely and effective communication is facilitated.

While participating in DemStepCare, patients continue to be cared for by their GPs, who can repeatedly take part in dementia-specific training sessions as the project progresses.

#### Description of control condition 1

GPs assigned to the control group 1 receive a shorter form of training. A case manager is employed and risk stratification is conducted, too, but the result has no influence on the further treatment of the patients, i.e. it only serves evaluative purposes. Neither the GPs nor the patients get to know the result of the stratification. There is a follow-up meeting with the case manager after nine months.

As there are small elements of intervention in control condition 1, control condition 1 cannot be considered as being merely usual care. However, the training of the GPs is intended as an incentive and the visits of the case managers are necessary to gather data for the evaluation. We therefore decided to use this slightly expanded usual care condition as control condition 1. Control group 2, the historical control condition, is inherently usual care.

Training of the GPs in intervention as well as in control condition 1 is carried out by experienced healthcare professionals. The case managers also receive training resulting in a certification as case manager according to the German Society for Care and Case Management (in German: Deutsche Gesellschaft für Care und Case Management, DGCC).

## Outcomes

The evaluation comprises a formative process evaluation and a summative evaluation. We thereby follow the recommendations for evaluating complex interventions [52]. Both types of intervention are aimed at both people who receive the DemStepCare intervention (patients and their caregivers), and people who provide the DemStepCare intervention (GPs and case managers). There are different points of measurements for different participants.

Due to the coronavirus pandemic, the delivery of intervention had to be suspended in April and May 2020. During this time, a nationwide lockdown was implemented in Germany, which applied from mid-March 2020 and was then successively lifted. In April and May 2020, participants of DemStepCare had access to a DemStepCare telephone helpline. No other elements of the intervention were offered for the safety of the patients. For this reason, it was decided to shift some points of measurement: If a person has undergone the two-month intervention pause, the t1-measurement will also take place two months later than originally planned (e.g., 11 months after t0 instead of nine months after t0 for PwD and caregivers).

### Process evaluation

Process evaluations aim at monitoring the feasibility and perceived success of the evaluated interventions. Relevant processes are identified, described and reported back to the involved parties.

The main questions of the process evaluation concern acceptance of, satisfaction with, and a benefit assessment of DemStepCare. Following a mixed-methods approach, data from caregivers and healthcare providers are collected via questionnaires and interviews. Patients are solely interviewed due to the assumed cognitive impairment and the associated stress possibly resulting from a written survey.

For the caregivers, an adapted version of the Perceived Involvement in Care Scale (PICS) [53, 54] is used to assess interaction with healthcare providers and involvement in care. In addition, new items will be developed in order to be able to precisely evaluate the satisfaction with the DemStepCare intervention. This survey takes place at baseline (t0) and at t1. A random sample of caregivers and patients (*N* = 20) will be additionally interviewed. The interviews will follow a semi-structured interview guide. Questions asked during the interviews will include “Were there situations or processes in DemStepCare that you experienced as difficult or worth improving?”; “How has your situation changed due to DemStepCare?” The interviews will be conducted at t1.

As the case managers are trained specifically for the project and become active in a new professional field, it will be assessed how their professional coping behavior, their stress management ability and their sense of coherence develop. Validated scales are used for this purpose: a scale to assess work-related behavior and experience patterns (in German: Arbeitsbezogenes Verhaltens- und Erlebensmuster, AVEM [55]), the Stress Management Questionnaire (in German: Stressverarbeitungsfragebogen, SVF [56]), and a scale to assess the sense of coherence (SOC) [57]. There are no English versions of the AVEM and SVF. The AVEM covers health-promoting or health-damaging behavior associated with professional requirements. This behavior is assigned to four patterns: health, protection, risk of overstraining oneself, and risk of chronic exhaustion and resignation. The SVF addresses different ways of coping with or processing stressful events (e.g. avoidance, distraction, and the need for social support). The SOC measures the extent to which people understand, manage and attribute meaning to what happens around them. There will be three measurements: one at baseline, i.e. before the case managers start work (t0_CM_), one after 12 months (t1_CM_), and one at the end of the intervention phase (t2_CM_). In addition, all the case managers are to be interviewed. The interviews will follow a semi-structured interview guide. Questions asked during the interviews will include “How do you experience the current care situation of your patients and their families?”; “How do you experience the collaboration with the GPs?” The interviews will start 20 months after the start of the intervention.

All GPs are interviewed in a panel survey. The questions for the survey were specifically developed for DemStepCare drawing on findings from our preliminary studies [58, 10, 59]. They contain both closed-ended and open-ended questions asking about satisfaction or dissatisfaction with different aspects of DemStepCare. There will be three measurements: one at baseline, i.e. before randomization and the first training session of the GPs (t0_GP_), one 12 months after completion of the first training (t1_GP_), and one at the end of the intervention phase (t2_GP_). A random sample of GPs (*N* = 10) will be additionally interviewed. The interviews will follow a semi-structured interview guide. Questions asked during the interviews will be similar to those used for the case managers, except that GPs will be asked about the collaboration with the case managers. The interviews will be conducted at t1_GP_.

### Summative evaluation

The summary evaluation examines the primary endpoints (i.e., quality of life of PwD, caregiver burden, and days spent in hospital) and various secondary endpoints, which are described below.

In order to compare the intervention group and control group 1, these two groups are examined at t0 (baseline) and t1 (=minimum duration of the intervention, 9 months after t0). In the intervention group, the intervention will also continue to be offered throughout the treatment period until t2 (= end of intervention; max. 27 months), so that the individual treatment courses in the intervention group can be further investigated. The intra-individual and longitudinal analyses in this group allow the predicting of the effectiveness of the treatment more precisely.

#### Primary endpoints

The three primary endpoints are assessed via questionnaires. An overview is shown in Table 1.

**Table 1 Tab1:** Primary endpoints

Construct	Respondents	Instrument at a given time		Group comparison
		t0	t1	
Quality of life (patients)	Patients and caregivers IG+ CG1	Quality of Life in Alzheimer’s Disease (QOL-AD) [60]	QOL-AD	IG vs. CG1
Caregiver burden (caregivers)	Caregivers IG + CG1	Berlin Inventory of Caregivers’ Burden with Dementia Patients (in German: Berliner Inventar zur Angehörigenbelastung – Demenz, BIZA-D) [61]	BIZA-D	IG vs. CG1
Days spent in hospital (patients)	Patients and caregivers IG + CG1	Original item	Original item	IG vs. CG1

*IG* intervention group, *CG1* control group 1, t0 = study inclusion, t1 = minimum duration of the intervention / nine months after t0

To measure the patients’ quality of life, we use the Quality of Life in Alzheimer’s Disease (QOL-AD), a validated scale developed specifically for PwD [60]. The QOL-AD encompasses 13 areas of life that need to be evaluated (e.g. family, living conditions, energy). There is a version for patients and a proxy version. In DemStepCare, we use both versions, with the proxy version being filled in by the caregivers. Both scores are integrated into a total score. There is one baseline measurement (t0) and one measurement at t1.

To measure the caregiver burden, we use the short form of the Berlin Inventory of Caregivers’ Burden with Dementia Patients (in German: Berliner Inventar zur Angehörigenbelastung – Demenz; BIZA-D) which was specifically designed and validated to measure the burden resulting from caring for a person with dementia [61]. The BIZA-D is a comprehensive instrument that, among other things, queries various care tasks and associated burdens, the social support experienced, and acceptance of the situation. Caregivers fill in the BIZA-D at baseline (t0) and at t1.

To measure the days spent in hospital, we use a self-developed item at t0 and t1. We ask for days spent in hospital in the last nine months. We use one version for patients and one proxy version for caregivers. In addition, we will receive individual level data from the participating health insurance companies for the inpatient treatment days. Since only a part of the participants will presumably be insured with these health insurance companies, we will use this data for plausibility checks (comparison self-report vs. claim data). The main data basis for the primary endpoint will be provided by the questionnaires.

#### Medication analyses

Within the multi-professional concept, clinical pharmacists conduct structured medication reviews at t0, t1 and t2. In the intervention group, additional medication analyses are performed quarterly and in case of crisis.

The quality of the prescribed medication is primarily measured by the Medication Appropriateness Index (MAI), an implicit prescriptive quality measure with good inter-rater and intra-rater reliability [62, 63]. The index provides ten criteria relevant for appropriate prescription, formulated as questions regarding indication, efficacy, dosage, correct dosage regimens, practicable directions for use, drug-drug interactions, drug-disease interactions, duplicate prescriptions, treatment duration and cost [62].

For a standardized evaluation of the criteria by the evaluators, the MAI-Score provides general instructions for the use of the index, precise definitions for each criterion and specific instructions and examples for answering the ten questions [62].

The evaluation of the criteria results in a weighted point score that represents the adequacy of each prescribed drug [63]. Only nine of the ten criteria of the MAI are used in DemStepCare, the question of economic efficiency of the prescription has been excluded.

In addition to the MAI, the following aspects are also addressed within the medication review to assess and evaluate safety and quality of medication:
underuse of medication for diseases requiring therapy using the START criteria [64]unsuitable drugs for geriatric patients based on the PRISCUS-list [65], FORTA-list [66] and STOPP criteria [64]reduction of multimedication using defined deprescribing strategiesthe number of drug-related problems according to PCNE version 9.0

The required information is retrieved from the electronic case record. Available clinical data (diagnoses, laboratory values) are included in the analysis. The implementation rate of pharmaceutical recommendations in the intervention group is determined based on the update of patient records.

#### Risk stratification of home care constellation

The regular assessment of risks in home care is a central component of the DemStepCare intervention, since the further course of treatment in the intervention group is based on the results of this assessment. The DSV is used for this purpose [47]. Its data concerning stability of care will also be integrated as a secondary endpoint in the evaluation.

#### Hospitalization

Besides the primary endpoint “days spent in hospital” (intervention group vs. control group 1), two additional secondary endpoints are related to hospital stays: Firstly, a comparison of days spent in hospital is also made between the intervention group and control group 2. For this purpose, the health insurance companies involved in the project provide data for control group 2. Secondly, the number of hospital stays is also analyzed (without considering the length of each stay), both between the intervention group and control group 1 and between the intervention group and control group 2. As with the hospital days, data is available either via questionnaires (intervention group and control group 1) or from aggregated data from the health insurance companies (control group 2) as well as for a small percentage of individual data from the health insurance companies (intervention group and control group 1).

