### Trial design

In a prospective, cluster randomized trial, two types of primary dementia care will be compared to each other: the innovative complex intervention DemStepCare (intervention group) and a slightly expanded usual care condition (control group 1). In addition, a second (historical) control group will be formed, which will be composed of aggregated routine data from health insurance companies involved in the project (control group 2).

A total of 120 GP practices are to be included for the intervention group and control group 1. Randomization with a 1:1 ratio is undertaken at the level of GPs’ practices and stratified by dementia sensitivity of the GPs. 800 PwD are to be included per group (i.e. intervention group, control group 1, control group 2).

Measurement times for PwD and caregivers are t0 (=time of inclusion) and t1 (=minimum duration of the intervention / nine months after t0). In addition, in the intervention group the further course of treatment is examined longitudinally and included in the evaluation (t2 = end of intervention / max. 27 months after t0).

The design of the study is shown in Fig. 1.

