## Methods: participants, interventions, and outcomes

### Study setting

The catchment area of DemStepCare is in a largely rural area of Rhineland-Palatinate, Germany. The outpatient clinic is located in the middle of the recruitment area at Rheinhessen Fachklinik Alzey, Landeskrankenhaus (AöR), allowing all patients of the intervention group to be reached.

Control group 2 will be composed of patients from all over Germany.

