### Eligibility criteria

Patients and (if possible) their caregivers are eligible to participate in the intervention group or control group 1, if they meet the following criteria:
Diagnosis of dementiaPlace of residence within the study areaInformed consent to participate in DemStepCare

Living in a nursing home is defined as an exclusion criterion.

As patients can only be included via their GPs, the patients must be cared for by a GP who participates in DemStepCare. The only requirement for participating GPs is that their practice must be within the study area.

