### Strengths

One of the strengths of the study is the multimodal approach that involves various actors in DemStepCare. Qualitative and quantitative data will be collected, the latter supplemented by routine data from the participating health insurance companies. By adopting a multimodal approach, we follow the recommendations for the evaluation of complex interventions [79].

Another methodological strength is the cluster randomized design and the use of two control groups. In control group 1 we are able to exploit all the possibilities of data collection that we also use in the intervention group. Control group 2, on the other hand, provides us with data that reflects current usual dementia care in Germany.

In terms of content, the importance of the caregivers is particularly noteworthy. While two of our three primary endpoints are patient-related, the third relates to the caregivers’ experienced burdens. In addition, other secondary endpoints relate to the caregivers. Family caregivers are key players in primary dementia care [4]. Their health is associated with the stability of the care situation [44]. In DemStepCare, this central aspect is taken into account and considered in the evaluation.

In summary, the DemStepCare intervention brings together promising aspects which are potentially useful in the primary care of PwD and their caregivers. A comprehensive process and outcome evaluation will help to assess the effectiveness of the intervention.

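### Days in hospital against control group 2 compares unlike measurements in unlike populations, so a difference can arise without an intervention effect and should be treated as descriptive

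*Protocol article*

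**What the plan says.** The Hospitalization section of the protocol article makes this a listed secondary endpoint: "a comparison of days spent in hospital is also made between the intervention group and control group 2". On sources, it says that "data is available either via questionnaires (intervention group and control group 1) or from aggregated data from the health insurance companies (control group 2"), and adds that individual insurer data exist for a small percentage of the two trial arms.

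Table 2 fixes the pairing for the days row: a study-specific item from patients and caregivers in the intervention group, and aggregated insurer data in control group 2, both at t0 and t1. The item is described under Primary endpoints: "We ask for days spent in hospital in the last nine months". The same section says of individual claims for inpatient days that "we will use this data for plausibility checks (comparison self-report vs. claim data"). Table 2 lists individual claims in the admissions row but not in this days row.

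On who is compared, Trial design says "a second (historical) control group will be formed" and Study setting says "Control group 2 will be composed of patients from all over Germany". The eligibility criteria are stated for the intervention group and control group 1 only, and end with "Living in a nursing home is defined as an exclusion criterion". The Strengths section says that control group 2 "provides us with data that reflects current usual dementia care in Germany". The Limitations section does not mention it.

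Under Health economic evaluation, the cost reduction attributed to the intervention is calculated against both control groups.

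**The concern.** A comparison with an external control needs the outcome to be measured in the same way on both sides, in comparable people, over comparable time. Here all three differ, and the article describes nothing that would remove the differences. The regression models under Statistical methods are set out for the three primary comparisons with control group 1. Aggregates do not allow adjustment at patient level.

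At stake is the reading of one secondary endpoint and of the cost evaluation. Control group 1 is acknowledged to be slightly more than usual care, so control group 2 is the only pure usual-care reference. Readers will be inclined to take a difference from it as the effect against usual care, and the cost section would carry that difference into net costs.

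**Working it through.** **1. The plan's own figures.** No sample size is given for the comparison with control group 2. The one given, for control group 1, reproduces. With d = 0.30, two-sided alpha 0.05/3 and power 0.80, the t-test formula gives 234.1, hence 235 per group. The design effect is 1 + 0.01 × 14 = 1.14, and 235 × 1.14 = 267.9, hence 268. After one-third dropout, 800 × 2/3 = 533 patients per group remain.

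**2. The two sides, as the article fixes them.**

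| Feature | Intervention group | Control group 2 |
|---|---|---|
| Days measured by | Self- or proxy-reported item, nine-month recall (Primary endpoints, Table 2) | Aggregated insurer data (Table 2) |
| Criteria | Study area, consent, competency to consent, not in a nursing home (Eligibility criteria, Interventions) | None stated |
| Region | Largely rural part of one federal state (Study setting) | Nationwide (Study setting) |
| Period | Includes the 2020 lockdown; t1 moved from 9 to 11 months for those affected (Outcomes) | Historical; calendar dates not given (Trial design) |
| Missing data | One-third dropout expected; selective loss conceded (Sample size, Limitations) | Does not depend on completing a questionnaire |

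Table 2 defines t0 as study inclusion, an event that a claims group does not have. For patients with the shifted t1, a nine-month recall leaves 11 − 9 = 2 months after t0 outside the window.

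**3. What a mismatch does when there is no effect.** Let r be the fraction of true days that the questionnaire captures, and p the proportional reduction in days due to calendar period in the intervention group only. The article gives neither.

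- A t1-only contrast gives an apparent ratio of r × (1 − p). Purely as illustration, r = 0.8 and p = 0.15 give 0.68. With over-reporting (r = 1.1) and p = 0 it is 1.10. The sign depends on inputs that the article does not contain.
- A contrast of t1/t0 ratios gives (r1/r0) × (1 − p), where p now acts at t1 only. If reporting is constant, r cancels. If it moves from 0.9 to 0.8, 0.8/0.9 = 0.89 remains. The calendar factor does not cancel.

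**4. How easily an artefact would look like a finding.** Assume 533 intervention patients (533/1.14 = 468 effective), 800 in control group 2, a two-sided 5% test and no true effect. The article specifies no such test.

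- In standard deviation units, SE = √(1/468 + 1/800) = 0.058. An artefact of 0.05, 0.10, 0.15, 0.20 or 0.30 SD is significant with probability 0.14, 0.40, 0.73, 0.93 or 0.999.
- On a negative binomial scale with mean m, dispersion k and the intervention mean m1 reduced by the artefact, SE of the log ratio = √((1/m1 + k)/468 + (1/m + k)/800). For assumed m of 3 to 8 days and k of 4 to 8, artefacts of 10%, 20% and 30% are significant with probability 0.10–0.15, 0.26–0.47 and 0.56–0.85.

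**The case against.** The strongest reply has four parts.

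- **The plan contains a check.** Individual claims for some participants will be compared with their self-reports. This stands in part: the check can reveal recall error, but the article does not carry the result into the comparison with control group 2.
- **t0 data are planned on both sides.** A constant reporting fraction would cancel in a change analysis. This stands, and it forms part of the fix. The article does not say that change is what will be compared, and cancellation does not remove a calendar effect.
- **A condensed article may leave the calendar window, restrictions and standardisation to the full protocol or the insurer specification.** This stands for those details, and their absence is not counted here. The unlike data sources and the historical, nationwide make-up of control group 2 are stated in the article itself.
- **The comparison is secondary, and no test or decision rule is attached to it.** This stands and limits the consequence. It does not remove the use in the cost evaluation or the silence in Limitations.

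A reader might go further and infer that the mismatches all favour the intervention. The documents do not support that. The error of the recall item is unknown in either direction. Control group 2 is not said to predate the pandemic or to include nursing-home residents. Nor is the effect of leaving such residents out of one side obvious, since the article's own background links crises in home care to admission. A reader might also see a contradiction in the group being historical in one section and reflecting current care in another; loose wording explains it equally well.

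**Conclusion.** The concern holds in a limited form. As specified, the comparison of days in hospital with control group 2 differs in measurement, population and period, so a difference can arise without an intervention effect. Neither direction nor size can be determined from the article. The ratios and probabilities above rest on assumed reporting error, calendar effect, mean and dispersion; they show only that moderate artefacts would often look like results.

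The randomised primary comparison with control group 1 uses the same questionnaire in both arms and is not touched. The consequence is confined to this secondary endpoint and the part of the cost evaluation that relies on control group 2. It merits a change because most of the data needed are already planned.

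**What to change.** 1. Add to the days row of Table 2 the individual claims already expected for part of the intervention group. Report a claims-versus-claims comparison with control group 2, in patients of the same insurers, beside the questionnaire-based one.
2. Compare change from the t0 period, and state how the t0 and t1 periods are defined for control group 2.
3. Where the insurers can supply it, limit the control group 2 aggregates to people not in nursing homes, and obtain them by age, sex, region and calendar period so that the groups can be standardised. Calendar period matters most, because step 2 does not deal with it.
4. Label the comparison, and the cost reduction derived from it under Health economic evaluation, as descriptive. Draw no effect claim from either, and add control group 2 to Limitations.

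**Cost.** Steps 2 and 4 need only wording. Step 3 needs a revised request to the insurers, who may not be able to meet it in full. Step 1 costs precision. The article gives no share beyond a small percentage. If it were 10 to 30% of 800 (80 to 240 patients, an assumption), the 95% half-width against 800 controls, ignoring clustering, would be 1.96 × √(1/80 + 1/800) = 0.23 SD to 1.96 × √(1/240 + 1/800) = 0.14 SD, compared with 1.96 × 0.058 = 0.11 SD for the questionnaire-based comparison. The claims analysis should therefore stand beside that comparison and not replace it.
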